#### Secondary objectives and outcomes measure

The secondary objectives are to assess the effectiveness of the PACThe program in real-life conditions based on subgroups and to compare the observed effects (at various time points) with those observed in the original PACThe study at the same time points.

Secondary endpoints will be assessed with the SF-36 questionnaire global and subscale scores obtained at inclusion, end of program, 6, 12 and 18 months after end of program. Scores in subgroups (according to BMI, age, menopausal status, level of education, precariousness (assessed via EPICES score)) will also be assessed.

### Setting and eligibility criteria

Participants have been recruited through referral from French physicians prescribing thermal treatments (among participating centers). The thermal resorts also promote the program in their brochures and on their websites, so that patients and doctors are aware of it. Eligible participants are women aged 18 to 75 who have undergone breast cancer treatments such as chemo- and/or radiotherapy, in the absence of residual or progressive disease, and whose treatment has been completed (with the exception of hormone therapy). The exclusion criteria are defined as follows:

Progressive or metastatic cancer.Patient suffering from disability.Severe personality or eating disorders (craving, bulimia, etc.)Underweight (BMI < 18.5 kg.m-2) or severe to massive obesity (BMI > 35 kg.m-2).Refusal to participate.Contraindication to physical activity (whether cardiovascular or related to musculoskeletal pathology); lymphedema is not a contraindication.Participation in another clinical study.Insufficient knowledge or understanding of the French language to correctly complete a quality-of-life self-questionnaire or to answer a dietary questionnaire.The medical contraindications to thermal treatment validated by the Société Française d’Hydrologie et de Climatologie will be applied and are as follows:Severe alterations in general condition (progressive infectious conditions, renal or hepatic insufficiency, cirrhosis, respiratory insufficiency, etc.)Severe or acute hemorrhagic rectocolitis and Crohn’s disease.Severe immunodeficiencies.Recent phlebitis.Hypertension.

### Intervention and participant timeline

This study is based on the PACThe program [1] which consisted in a two-week follow-up care protocol of 13 days of intervention, averaging 4 sessions per day, along with all the required dietary meals each day. The interventions are defined as physical activity with endurance, muscle strengthening, and flexibility exercises and with aqua aerobic sessions. The participants were also provided with psychological support and self-esteem guidance.

At the start of the stay at thermal resorts and before the first treatment, selection criteria will be checked by the thermal doctor, who also provides initial patient information. After receiving and reading the information notice, the patient gives the signed non-opposition notice to the thermal doctor and keeps a copy before any study procedure. The thermal doctor collects the clinical and medical information required for the program (age, BMI, anti-cancer treatments received, surgery, menopausal status, precariousness, level of education) and enters it into the eCRF. The SF-36 questionnaire is given to the patient. A check-up at the start of the treatment is carried out by one of the health professionals on the program team.

At the end of the stay at the thermal resort, the doctor collects the clinical and medical information required for the program. The thermal doctor gives the patient the SF-36 questionnaire to fill in.

For the follow up at 6-12-18 months, the questionnaires are sent to the patient to be completed.

[figure not shown]

### Sample size

The main analysis consists in comparing the change in SF-36 global score at 6 months from baseline to the value obtained in the PACThe study control group (historical comparator). In the randomized PACThe study, the difference in SF-36 global score between the experimental and control groups was 2.2 points at baseline (*p* =.3), and 9.5 points at 6 months (effect size = 0.63, *p* <.001), with a difference between 6 months and baseline of 11.9 points in the experimental group, and 4.6 in the control group, and a standard deviation between 15 and 16.

To determine the number of subjects required, it is assumed that the variation between 6 months and inclusion in this study will be slightly lower than in the PACThe study: expected value of 10 points. It is also estimated that the variability of the scores obtained will be greater than that observed in the PACThe study. Thus, a sample size of 400 should allow us to show a reasonable effect size of 0.2 (alpha risk equal to 5% and 95% power, for a one-sample Student’s t-test), and compensate for an estimated 15–20% drop-out rate.

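### The 95% power belongs to a test against a fixed 4.6 points, but the main analysis compares with the PACThe control arm, whose 4.6 is itself an estimate

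*Protocol article*

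**What the plan says.** The protocol article's Sample size section defines the main analysis as the 6-month change in the SF-36 global score set against the PACThe control group, which it calls a historical comparator. It reports the earlier randomised trial's results "with a difference between 6 months and baseline of 11.9 points in the experimental group, and 4.6 in the control group". The spread it quotes for that trial is "a standard deviation between 15 and 16". For the new cohort it assumes an "expected value of 10 points" and adds: "It is also estimated that the variability of the scores obtained will be greater than that observed in the PACThe study". No figure is given for that larger variability. It concludes that "a sample size of 400 should allow us to show a reasonable effect size of 0.2". The design settings behind this conclusion are "alpha risk equal to 5% and 95% power, for a one-sample Student’s t-test". The same number is meant to "compensate for an estimated 15–20% drop-out rate".

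The Statistical analysis section repeats the comparison with the control group's value, names a Student's t-test without saying one-sample or two-sample, and excludes patients with no 6-month questionnaire. The Discussion describes the aim as a comparison of two groups. The Background gives the earlier trial's total size, 251 patients, but not the size of its control arm.

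**The concern.** A one-sample t-test allows for sampling error in the new cohort only. The 4.6 points are the observed mean change in one arm of a trial that, as a whole, was smaller than the planned 400. With similar SDs, that arm's mean is less precise than the mean of the new cohort, so the test leaves out the larger of the two error terms.

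Two things are at stake. The stated power is not the power of the comparison the article says it will make. And if the test is run as sized, it will find a difference from the control group too often when there is none. This is the primary analysis, and its purpose is to confirm benefit.

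**Working it through.** **Inputs from the article.** Alpha 5% (sidedness not stated), power 95%, effect size d = 0.2, expected change 10, control change 4.6, SD 15–16, drop-out 15–20%. Evaluable patients: 400 × 0.80 = 320 to 400 × 0.85 = 340.

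**Assumptions of this check.** 125 control patients (about half of 251), with 80 as a low case and 250 as an impossible upper bound. Control SD of the change 15.5. New-cohort SD 15.5, 20 or 27.

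**1. The plan's own figure.** Normal approximation, two-sided: n = ((1.960 + 1.645)/0.2)² = 325; with the t distribution, 327. Allowing for drop-out, 327/0.85 = 385 and 327/0.80 = 409, so 400 reproduces. Power at d = 0.2 is 94.6% with 320 patients and 95.7% with 340. A one-sided test would need 272 evaluable, or 320–340 with drop-out, so the two-sided reading is the one that fits.

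**2. Where 0.2 lies.** The expected difference is 10 − 4.6 = 5.4 points. 5.4/16 = 0.34 and 5.4/15 = 0.36. An effect of 0.2 equals 5.4 points only at SD = 5.4/0.2 = 27. Planning for 0.2 is therefore stricter than the quoted inputs require.

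**3. Power at d = 0.2 with control error counted, equal SDs.** Noncentrality = d/√(1/n_new + 1/n_control).
- 125 controls, 320 new: 0.2/√(0.003125 + 0.008) = 1.90, power 47%. With 340 new: 48%.
- 80 controls: about 36%.
- 250 controls: 66–67%.
- 125 controls and an unlimited new cohort: Φ(0.2√125 − 1.96) = Φ(0.28) = 61%.

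**4. Power for the expected 5.4 points.** Welch test, SE = √(SD_new²/n_new + 15.5²/n_control). The SE column is for 320 new patients and 125 controls; the power ranges cover 320–340 new patients.

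| New SD | SE | Power, 125 controls | Power, 80 controls |
|---|---|---|---|
| 15.5 | √(0.751 + 1.922) = 1.635 | about 91% | about 79% |
| 20 | √(1.250 + 1.922) = 1.781 | about 86% | 74–75% |
| 27 | √(2.278 + 1.922) = 2.049 | 75–76% | 65–66% |

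**5. Type I error if 4.6 is treated as fixed.** Suppose the true mean changes are equal. Over repeated sampling of both groups, the two-sided rejection rate is 2Φ(−1.96 × SE_new/√(SE_new² + SE_control²)). With 125 controls, SE_control = 15.5/√125 = 1.386.
- New SD 15.5, 320 patients: SE_new = 0.866, ratio 0.866/1.635 = 0.530, error 30% (31% with 340).
- New SD 27, 320 patients: SE_new = 1.509, ratio 1.509/2.049 = 0.737, error 15%.

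**The case against.** The article ties its 95% explicitly to a one-sample t-test, and for that test the figure is true. If 4.6 is meant as a fixed benchmark, nothing is miscalculated. That stands as a statement about the named test. It does not make the result a comparison with the control group, which is how the Sample size, Statistical analysis and Discussion sections all describe it.

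A reader might infer that 0.2 is an arithmetic error, because the quoted inputs give 0.34–0.36. The article does not support that. It presents 0.2 as an effect the sample can show, not as the quotient of 5.4 and an SD, after saying that it expects greater variability. The SD of 15–16 may also be that of scores rather than of change, since 9.5/0.63 = 15.1. With zero correlation between visits, the SD of change would then be about 21–23 and d about 0.24–0.255, closer to 0.2. The choice over-sizes the one-sample test, which needs only 103–117 evaluable patients for 5.4 points at SD 15–16. The unstated SD is mostly detail that the full protocol may hold.

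The control-arm size is also not in the article, so every two-sample figure here is conditional on an assumed n.

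**Conclusion.** The concern holds for the power claim and the test, not for the sample size. The 95% is valid only if 4.6 points is an error-free constant. As a comparison with the control arm, power at d = 0.2 is about 47–48% (125 controls assumed, equal SDs) and stays below 70% even with 250 controls, so the conclusion does not depend on the assumed arm size.

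A reader might take 47–48% as the study's real power and conclude that 400 is too few. That goes too far. Under equal SDs, d = 0.2 means 5.4 points only if the control SD is also 27, which contradicts the reported 15–16. For the expected 5.4 points with 125 controls and control SD 15.5, power is about 75–91% over new-cohort SDs of 27 down to 15.5. N = 400 is defensible.

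The inflated error rate, about 30% with equal SDs and about 15% with a new SD of 27, is the more consequential result if the test is run against a fixed 4.6. This should be fixed, but it does not undermine the design.

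**What to change.** Keep N = 400. Specify the primary test as a two-sample (Welch) comparison using the PACThe control arm's mean change, its SD and its number of evaluable patients. Restate the power for a 5.4-point difference with an explicit SD of the change, 320–340 evaluable patients and the actual control n.

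Alternatively, keep the one-sample test, declare 4.6 points a fixed benchmark and justify it. Then limit both the 95% power and the conclusion to exceeding that benchmark, and drop the wording that presents the result as a comparison with the control group.

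Cost: the Sample size and Statistical analysis paragraphs and one sentence of the Discussion change, and no patients are added. The first option needs the control arm's summary statistics and gives a less favourable stated power. A two-sample version of the non-parametric fallback would need individual control data. The second option costs strength of claim.

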### Statistical analysis

The main analysis consists of comparing the change in SF-36 global score [3] between 6 months and baseline with the value obtained in the PACThe control group (historical comparator) using a Student’s t-test (or a non-parametric test depending on the data distribution). All patients who will not respond to the questionnaires at 6 months will be excluded from the analysis.

The evolution of the SF-36 global score over time (repeated data) will be analysed using mixed-effects linear regression models, followed, in the event of a statistically significant result, by post-hoc pairwise comparisons at different time points, with correction for multiple comparisons).

Confidence interval estimates of observed effects (changes in measurements at different time points post-program vs. baseline) will be used for comparison with the effects observed in the PACThe study, as well as analysis in subgroups defined by age, menopausal status and type of anti-cancer treatment.

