## Discussion

This study will examine the improvement of quality of life at six months after a 3 week post-therapy rehabilitation program in thermal resorts for breast cancer women in complete remission (PACThe program) in real life (regardless of their treatment or the time between the end of treatment and the start of the program). The program PACThe has demonstrated that rehabilitation program based on a stay at thermal resort allowed a significative improvement of the quality of life, functional capacities, depressive situations, sleep, weight control, level of physical activity in previously active patients, and the return to work. This study aims at validating those effects in real life conditions by comparing the experimental group to the control group used in the PACThe program. A number of relevant publications have demonstrated that thermal therapy can complement conventional therapies for rheumatic diseases [11], and it was also described through a review that thermal therapy, hydrotherapy and balneotherapy have positive effects on sleep quality [12]. However, description of that kind of rehabilitation program for cancer survivors has been very poor. Even though only women will be enrolled, this trial will determine the extent to which a post-cancer thermal therapy improves the way patients go back to their life after their remission. Real-life studies offer the advantage of reflecting current clinical practices, allowing to evaluate how treatments perform in real clinical settings. These studies have less strict criteria for patient selection, which means they include a more diverse group of patients, resembling the variety of people seen in real-life clinical settings. Therefore, the results of this observational trial will likely be useful for the development of such care pathway for breast cancer survivors, but also for other cancer survivors.

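### The primary test treats the PACThe control-arm change of 4.6 points as a known constant, so for a comparison with that control group its standard error is too small and its power overstated

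*Protocol article*

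**What the plan says.** The Sample size and Statistical analysis sections both define the main analysis as the cohort's change in SF-36 global score from baseline to 6 months, set against the PACThe control group. In Statistical analysis the comparison is "with the value obtained in the PACThe control group (historical comparator"), made "using a Student’s t-test (or a non-parametric test depending on the data distribution"). That section does not say whether the test has one sample or two.

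The Sample size section does. It plans 400 patients for a standardised effect of 0.2 with "alpha risk equal to 5% and 95% power", "for a one-sample Student’s t-test", and allows for 15–20% dropout. It reports the PACThe changes at 6 months as 11.9 points (experimental) and 4.6 points (control) with an SD of 15 to 16, expects 10 points in the new cohort, and expects more variability than in PACThe.

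The Discussion says the effects will be validated "by comparing the experimental group to the control group used in the PACThe program". The Abstract (Methods) describes the main analysis differently, as the 6-month score against the baseline score, with no PACThe comparator.

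**The concern.** A one-sample t-test puts the sampling error of the new cohort in the denominator and nothing else. That is right when the reference is a fixed threshold chosen in advance. Here the reference is an observed mean from one arm of a trial of 251 patients, so it has a standard error of its own. That arm is probably much smaller than the new cohort, so its standard error is of the same order as the cohort's.

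If the conclusion is to be that women in the programme improve more than the PACThe controls did, a low observed mean in the old control arm, arising by chance, can produce a significant result with no programme effect. The study has no concurrent control, so its main inference rests on this one comparison. The stated 95% power also describes a different comparison from the one the Discussion announces.

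**Working it through.** **Reproducing the planned size.** One-sample t-test, two-sided 5%, power 95%, d = 0.2. The normal approximation gives (1.96 + 1.645)² / 0.2² = 325, and the noncentral t gives 327. Allowing for dropout: 327/0.85 = 385 and 327/0.80 = 409. The planned 400 lies between them. A one-sided test needs 272, or 320 to 340 after dropout, and does not reach 400. So the trial was sized on a two-sided one-sample test with 4.6 fixed.

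**Inputs from the article.**
- Control change 4.6 and expected cohort change 10, a difference of 5.4.
- Implied cohort SD: 5.4 / 0.2 = 27.
- Analysed: 400 less 15–20% = 320 to 340; I use 330. Statistical analysis excludes patients without a 6-month questionnaire.

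**Assumptions, because the article gives no figure.**
- Control-arm size n0: about 125 (half of 251), range 80 to 167. The upper end is two-thirds of 251; the lower end is a 1:1 arm with about a third not evaluable. As a rough check, a baseline difference of 2.2 with p = .3 and SD 15–16 implies about 200 to 227 patients in all, or 100 to 114 per arm if 1:1.
- Control SD of change: 15.5. The article does not say whether 15–16 is the SD of the score or of the change, and 9.5/0.63 = 15.1 suggests the score.
- Cohort SD of change: 15.5, 20 or 27.

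**Formulas.** SE1 = SD1/√330. SE0 = 15.5/√n0. SE = √(SE1² + SE0²). For the null of equal population means, the two-sided error of the one-sample test is 2 × [1 − Φ(1.96 × SE1/SE)], and the false claim of benefit is half of that. Power for 5.4 points is Φ(5.4/SE − 1.96).

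**Results at n0 = 125** (SE0 = 1.39; 95% interval for the 4.6 itself about 1.9 to 7.3):

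| Cohort SD | SE1 | SE | SE/SE1 | Two-sided error | False benefit | Power, one-sample | Power, two-sample |
|---|---|---|---|---|---|---|---|
| 15.5 | 0.85 | 1.63 | 1.91 | 30% | 15% | >99% | 91% |
| 20 | 1.10 | 1.77 | 1.61 | 22% | 11% | >99% | 86% |
| 27 | 1.49 | 2.03 | 1.37 | 15% | 8% | 95% | 76% |

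A simulation with 200,000 runs, 327 analysed, 125 controls and control SD 16 gave two-sided errors of 30.1%, 23.0% and 15.7% for cohort SD 16, 20 and 27.

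**Varying the control-arm size** (cohort SD 15.5 / 20 / 27):
- n0 = 80: two-sided error 38.7 / 29.3 / 20.2%; two-sample power 80 / 75 / 66%.
- n0 = 100: 34.5 / 25.6 / 17.5%; power 86 / 81 / 71%.
- n0 = 167: 25.6 / 18.5 / 12.7%; power 96 / 91 / 81%.

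**A more favourable case.** Control SD of change 12, cohort SD 27, n0 = 125: SE0 = 1.07, SE = 1.83, two-sided error 11%, power 84%.

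**What this means in points.** With cohort SD 15.5, the one-sample test declares superiority once the observed change exceeds 4.6 + 1.96 × 0.85 = 6.3. That value lies inside the control arm's own 95% interval. The 95% half-width for the difference should be 3.2 points, not 1.7; at cohort SD 27 it should be 4.0, not 2.9.

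**The case against.** The strongest reply is that the test is valid as a test against a fixed benchmark: if the hypothesis is literally that the cohort's mean change equals 4.6, the error rate is 5%. That is correct. A reader might infer that the false-positive rate is simply several times 5%. The article does not support that as an unconditional fact: the inflated rates belong to a different null, equality with the PACThe control population, and average over the sampling error of the old control mean. But that null is the one the Discussion's group comparison needs, and 4.6 is not justified anywhere as a threshold in its own right.

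A second reply is that the inputs are missing. This stands as a reason to give ranges. If the SDs of change in both studies are smaller by the same factor, the error rate does not move, because only their ratio matters. If only the control SD is smaller, the problem shrinks, to about 11% in the favourable case above. Nor does the control arm always contribute at least as much variance as the cohort: at the implied cohort SD of 27 and 125 controls the ratio is 1.39²/1.49² = 0.87.

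Third, Statistical analysis names only a Student's t-test, and the Abstract compares with baseline. A test of zero change would not have this variance problem, but it would drop the control comparison. This shows that the sections need reconciling; it does not remove the one-sample test that Sample size names and that reproduces 400.

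Two wider readings are tempting and go too far. One is that the secondary intervals, which "will be used for comparison with the effects observed in the PACThe study", share the defect; the article names no test there and does not say that PACThe's uncertainty is ignored. The other is that the option of a test "or a non-parametric test depending on the data distribution" must be deleted; a rank test would set a median-type quantity against a mean, but no harm of any stated size follows, and the choice can be left to the analysis plan.

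**Conclusion.** The point holds in this form and should be corrected before the analysis, because it concerns the primary comparison. As written, the sampling error of the control-arm change is set to zero although the conclusion sought is about that control group. With about 125 controls, an SD of change near 15.5 in controls and 15.5 to 27 in the cohort, and about 330 analysed, the two-sided error for no difference from the PACThe control population is roughly 15–30%, and false claims of benefit run at about 8–15% against 2.5%. Over 80 to 167 controls the two-sided range is about 13–39%.

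On the plan's own implied SD of 27, power falls from 95% to about 76%. So if the planned 5.4-point effect is real, a properly specified test still succeeds more often than not. These figures cover sampling error only; any bias from controls who were neither concurrent nor selected in the same way is a separate matter and is not counted.

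**What to change.** - Define the primary analysis as a two-sample comparison of 6-month change: a Welch test and 95% confidence interval built from the PACThe control arm's mean, SD of change and number evaluable at 6 months. If individual PACThe data are available, use an ANCOVA of the 6-month score adjusted for baseline instead.
- State the control arm's SD of change and evaluable number in the plan, since the article gives neither.
- Restate the power in the Sample size section for that comparison. No further enrolment is proposed; the section should report the power that the planned 400 gives.
- Reconcile the Abstract's comparison with baseline with the Sample size and Statistical analysis sections, so that one primary hypothesis is stated throughout.
- Wherever a secondary result is formally compared with a PACThe effect, use the combined standard error.

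The cost is a change of wording and retrieval of the PACThe summary statistics or data. The price is a wider confidence interval (half-width about 3.2 to 4.0 points instead of 1.7 to 2.9, at 125 controls) and a lower stated power.

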#### Primary objective and outcome measure

The primary objective is to confirm the improvement in the quality of life at 6 months following the implementation of a post-therapeutic support and rehabilitation program for women in complete remission from breast cancer in thermal resorts (PACThe program), in real-life conditions, regardless of their treatment or the interval between the end of treatment and the start of the program.

The primary outcomes is the change in SF-36 global score [3] between baseline and at 6 months.

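### The optional switch of the primary test to a rank test would set a median-type quantity against a reference of 4.6 that behaves as a mean; with skewed change scores this gives an error of unknown direction

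*Protocol article*

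**What the plan says.** The endpoint is fixed under Primary objective and outcome measure: "The primary outcomes is the change in SF-36 global score" from baseline to 6 months. Under Statistical analysis, that change is compared with the PACThe control group's value by a t-test, "or a non-parametric test depending on the data distribution". The article names neither the alternative test nor what would trigger it.

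The only reference value is in Sample size, where the PACThe changes are reported as "11.9 points in the experimental group, and 4.6 in the control group, and a standard deviation between 15 and 16". The comparison there is made "to the value obtained in the PACThe study control group (historical comparator"), that is, with a single historical figure. The sample size is justified with "alpha risk equal to 5% and 95% power, for a one-sample Student’s t-test".

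**The concern.** A one-sample test needs a null value for the quantity it tests. The t-test concerns the mean change. The Wilcoxon signed-rank test concerns the pseudo-median and the sign test the median. These coincide when the distribution is symmetric and separate when it is skewed. The article supplies one reference, 4.6, and no control-group median or pseudo-median.

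Skewness is one of the main reasons an analyst would judge a t-test unsuitable. The switch can therefore happen in the very situation where 4.6 stops being the right reference. The primary conclusion would then depend partly on the shape of the distribution and not only on whether mean quality of life improved more than in the PACThe controls. Depending on the direction of skew, that could mean a benefit declared without a gain in the mean, or a real gain missed.

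**Working it through.** **Inputs from Sample size.** Reference 4.6; expected change 10; PACThe SD 15-16, with larger variability expected here but no figure given; effect size 0.2; alpha 5% (sidedness not stated); power 95%; N = 400; drop-out 15-20%.

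**Inputs assumed.** Two-sided test; signed-rank or sign test as the fallback; shifted gamma distributions for skewed change; SD 16 to 27. Under the null the rejection rates do not depend on the SD.

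**1. The plan's own figure.** Normal approximation: n = (1.96 + 1.645)² / 0.2² = 325; the exact t calculation gives 327. Inflated for drop-out: 327/0.85 = 385 and 327/0.80 = 409. N = 400 is reproduced. It leaves 400 × 0.80 = 320 to 400 × 0.85 = 340 women analysed, with t-test power at effect size 0.2 of 94.6% and 95.7%.

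**2. Is 4.6 a mean?** The article does not use the word. The group difference in PACThe "was 2.2 points at baseline" and 9.5 at 6 months: 9.5 − 2.2 = 7.3, and 11.9 − 4.6 = 7.3. Means add in this way; medians in general do not. Also 9.5/0.63 = 15.1, in line with the SD of 15-16. It behaves as a mean.

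**3. True mean change exactly 4.6, left skew, n = 320** (simulation, 3,000-5,000 trials per setting)

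| Skewness | Signed-rank rejects | of which favours programme | Sign test favours programme | t-test rejects |
|---|---|---|---|---|
| 0 (normal) | 5.4% | 2.7% | 2.7% | 5.5% |
| −0.3 | 7.3% | 6.5% | 10.1% | 5.3% |
| −0.5 | 11.3% | 11.1% | 21.9% | 4.9% |
| −0.75 | 20.0% | 19.9% | not run | 5.4% |
| −1.0 | 31.4% | 31.4% | 67.5% | 5.1% |

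The nominal rate in favour of the programme is 2.5%. Repeat runs put the signed-rank rejection rates at 7-8%, 10-12%, 19-20% and 31-32% for the four skewed rows.

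**4. Cross-check by hand.** At SD 16 the pseudo-median lies 0.4, 0.7, 1.0 and 1.3 points above the mean at these four skewness values. The standard error is 16/√320 = 0.894. P(Z > 1.96 − shift/0.894) gives about 6.5%, 12%, 20% and 31%, which agrees with the table.

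**5. Right skew.** The picture is mirrored. False benefit under signed-rank falls to 0.8%, 0.2% and 0.0% at skewness +0.3, +0.5 and +1.0. The cost is power: for a true change of 10 with SD 27 (5.4/27 = 0.2) and skewness +1, signed-rank power is about 52-58%, against about 96% for the t-test.

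**6. Symmetric but non-normal.** With t-distributed changes on 5 degrees of freedom, signed-rank declares benefit in 2.1-2.8% of null trials. There is no bias.

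**7. The switch itself.** If a Shapiro-Wilk test at 5% triggered it (assumed, n = 327), the switch would occur in 49%, 91% and 100% of trials at left skewness 0.3, 0.5 and 1.0. Benefit would be declared in 5.4%, 11.6% and 32.0% of null trials.

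**8. Does the t-test need a fallback?** At n = 320-340 its two-sided error is 4.6-5.5% across these distributions, including skewness 2. Its upper tail is 1.6-3.6%.

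**The case against.** The strongest reply is that the harm is conditional and may not arise. Several parts of it stand.

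- A reader might infer that the fallback is biased towards confirming the programme. The document does not support this: it gives no distribution, skewness or median of change, and right skew is no less compatible with it than left skew.
- The displacement is small in points: 0.4 to 1.3 at SD 16, against a planned margin of 10 − 4.6 = 5.4. At a true change of 10 and n = 320, for skewness of 0.5 or 1.0 in either direction, both tests reject in at least 99.8% of trials at SD 16. At SD 20 both reject in at least 98.8%, except signed-rank at skewness +1.0 (about 94-95%).
- A reader might infer that the fallback has no merit at all. For symmetric heavy-tailed data a rank test is valid and commonly more efficient.
- Stating power for the t-test alone is normal practice and no separate defect. The name of the fallback and its trigger may properly stand in a SAP that is not shown, so their absence is not the point.
- The article also plans confidence intervals for change from baseline, so an estimate would stand beside any rank p-value. That softens the problem but does not change the primary test.

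What does not stand is the argument that the SAP may settle it. A switching rule would say when the rank test is used; it would not make 4.6 the right reference for that test.

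**Conclusion.** The concern holds as a conditional mismatch. If change scores are skewed and the primary test is switched to a one-sample rank test, 4.6 is the wrong reference, and the error can go either way. With no benefit on the mean, left skewness of 0.3 to 1.0 takes signed-rank rejection to about 7-32%, nearly all of it in favour of the programme from 0.5 upward. Right skew removes false benefit but at skewness +1 and effect size 0.2 cuts power from about 96% to about 52-58%.

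The upper figure of 32% is not this trial's expected error rate. It assumes a true mean change of exactly 4.6, skewness −1 and a signed-rank test, none of which the article states. The risk matters most when the true gain over the controls is small or absent, or when variability is well above the PACThe figure. Confidence is high in the mechanism and low in any particular size. Treating 4.6 as known without error is a separate matter, not assessed here.

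**What to change.** Delete the parenthesis. State that the primary analysis compares the mean 6-month change with the PACThe control mean by a t-based test with a 95% CI, whatever the distribution. Report a bootstrap CI for the mean change, and any rank test, as sensitivity analyses only.

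This costs one sentence in the protocol and the SAP, made before the data are analysed. No further data or patients are needed, and N = 400 (327 evaluable) is unchanged. The downside is small: some lost efficiency if the changes prove symmetric and heavy-tailed.
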